**Table 3. Supplemental Insulin Dose Adjustment Plan**

| Prior meal Blood Glucose levels (mg/dL) | Current meal blood glucose level (mg/dL) | Supplemental Insulin dose (SID) |
| --- | --- | --- |
| greater than 130 | 80-130 | Interpretation: correct SID  Instruction: nothing to do |
| greater than 130 | less than 80 | Interpretation: SID is too high  Instruction: increase sensitivity factor by 10 |
| greater than 130 | greater than 130 | Interpretation: SID is too small  Instruction: decrease sensitivity factor by 10 |

**C. Basal Insulin adjustment plan:** Basal detemir injection will be given consistently at bedtime once a day. Subjects will titrate their long-acting insulin analog (detemir) dose every third day, to achieve a fasting plasma glucose of 90-120 mg/dL using the algorithm shown in Table 2 below. We will aim to maintain participants on a total daily **basal** insulin dose of 0.3-0.8 U/kg/day or higher if necessary, given once daily at bedtime. This will ensure relative normal inter-prandial glycemia and the achievement of our HbA1c targets.

**D. Metformin or Placebo:** All participants will be provided with a 3 month supply of metformin or placebo at baseline, +3, and +6mo. Subjects will be advised to start at one capsule daily for 2 weeks, and then increase to 2 capsules once daily for the remainder of the study duration.

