**Table 2. Summary of Expected Blood Glucose Levels at Different Times of the Day**

| Time | Before breakfast | Before lunch or dinner | Before bedtime | 2 hours after a meal | At 3AM |
| --- | --- | --- | --- | --- | --- |
| Expected Glucose level (mg/dL) | 90-120 | 80-130 | greater than 100 | less than 220 | greater than 100 |

**A. Bolus insulin dose adjustment plan:** All participants will be placed on treat-to-target regimen plus either metformin or placebo as described below. The insulin boluses for meals will be calculated from an insulin to carbohydrate ratio that would be predetermined by the endocrinology team for each patient. We will strive to maintain a basal : bolus insulin ratio of 1:1, i.e., each component will constitute 50% of the total daily dose of insulin. Our goal is to maintain a premeal blood glucose level of 90-130 mg/dL. To adjust premeal bolus doses, we will focus on the pattern of blood glucose levels before lunch, dinner, and bedtime. If the blood glucose levels at the same time of day (e.g., before dinner) are high **two days** in a row, we will increase the preceding premeal (e.g., before lunch) bolus by 10 percent. Conversely, we will decrease a preceding premeal bolus by 10% if a **single** low blood glucose is obtained before a meal. Changing this bolus dose the very next day will prevent a recurrence of hypoglycemia and thereby protect against the establishment of reduced hypoglycemic awareness[60]

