**B. The correction factor or supplemental insulin dose adjustment plan:** The correction factor or supplemental insulin is the amount of fast-acting insulin that is added or subtracted from the insulin boluses to maintain euglycemia 2 hours after a meal as shown below in Table 3. The formula for the correction factor is (BG-X)/ISF, where BG is current blood glucose, X is ideal blood glucose for the patient, and ISF is insulin sensitivity factor. ISF will be calculated using the 1500 Rule, i.e., 1500 divided by the total daily dose of insulin. Our goal is to maintain a 2-hour post-prandial glucose level of <180 mg/L. To analyze the accuracy of the supplemental doses, we will look at every high blood glucose level and the level immediately following it. Specifically, if every high blood glucose level is followed by one in the target range, this indicates that the patient’s supplemental dose is correct. However, if most high blood glucose levels are followed by hypoglycemic levels, then the supplemental dose is too high. Conversely, if most high levels are followed by another high level, then the supplemental dose is too low. We will advise the participant to decrease or increase the sensitivity factor in the supplemental formula as needed to achieve the desired change in the blood glucose level as shown in Table 3.

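### Table 3 lowers the insulin sensitivity factor by 10 with no unit, scaling, floor or cap; read as a flat 10, one step doubles the correction dose at 75 U/day and triples it at 100 U/day

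*Protocol*

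**What the plan says.** The plan for correction (supplemental) insulin is in the Visit III procedure, part B, and in Table 3.

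- Dose: "The formula for the correction factor is (BG-X)/ISF", where BG is the current glucose and X the patient's ideal glucose.
- Starting ISF: "ISF will be calculated using the 1500 Rule, i.e., 1500 divided by the total daily dose of insulin".
- Trigger for a larger dose: "if most high levels are followed by another high level, then the supplemental dose is too low".
- Who acts: "We will advise the participant to decrease or increase the sensitivity factor in the supplemental formula as needed", with Table 3 giving the change.
- Size of the change when a reading above 130 mg/dL is followed by another above 130: "Instruction: decrease sensitivity factor by 10". The mirror rule raises ISF by 10 when the next reading is below 80.

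The neighbouring rules are built differently. For meal boluses (part A), "we will increase the preceding premeal (e.g., before lunch) bolus by 10 percent". Basal detemir moves by 2 units (titration algorithm for detemir). The expected dose level comes from part C, a basal "insulin dose of 0.3-0.8 U/kg/day or higher if necessary, given once daily at bedtime", and from part A: "We will strive to maintain a basal : bolus insulin ratio of 1:1". The inclusion criteria also list a requirement above 2 U/kg/day under the type 1 route.

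**The concern.** ISF is the divisor in the dose formula, and under the 1500 Rule it shrinks as TDD rises. Taking a fixed amount off a shrinking divisor enlarges the dose disproportionately. The effect is greatest in participants on the most insulin, and this trial sets out to enrol insulin-resistant youth aged 10 to 18. Assessments for Safety names hypoglycemia as the main safety concern. Table 3 is the only place that gives a step size for the correction factor, so what it says is what staff and families would apply.

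**Working it through.** **Inputs.** From part B: dose = (BG − X)/ISF and ISF = 1500/TDD. From Table 3: ISF falls by 10. Glucose is in mg/dL and the dose in units, so ISF is in mg/dL per unit, and a flat 10 in that unit is the natural reading. The protocol states no multiplier, so there is no figure of its own to reproduce.

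**Multiplier for one decrease**, with BG − X held fixed and ISF still at its 1500-Rule value:

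m = ISF/(ISF − 10) = (1500/TDD)/(1500/TDD − 10) = 150/(150 − TDD)

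| TDD (U) | ISF before → after | m |
|---|---|---|
| 24 | 62.5 → 52.5 | 1.19 |
| 60 | 25 → 15 | 1.67 |
| 75 | 20 → 10 | 2.00 |
| 100 | 15 → 5 | 3.00 |
| 120 | 12.5 → 2.5 | 5.00 |
| 150 | 10 → 0 | undefined |

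Above 150 U, ISF turns negative. At 75 U a second step takes ISF from 10 to 0. With assumed BG 250 and X 120, the dose goes from 130/20 = 6.5 U to 130/10 = 13 U at TDD 75, and from 130/15 = 8.7 U to 130/5 = 26 U at TDD 100.

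**Are such TDDs in scope?** Basal 0.3 to 0.8 U/kg/day with an equal bolus share gives 0.6 to 1.6 U/kg/day in total, or more where needed. The protocol gives no weights, so these are assumptions:

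- At 1.6 U/kg/day, m = 2 is reached at 75/1.6 = 46.9 kg and m = 3 at 100/1.6 = 62.5 kg.
- At 2 U/kg/day, they are reached at 75/2 = 37.5 kg and 100/2 = 50 kg.

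**When would a step overshoot?** Illustration only: linear response, same starting glucose, neutral meal bolus. Suppose a reading of 220 was previously corrected to L. A decrease is triggered if L > 130. After the step the predicted glucose is 220 − m(220 − L), which is below 80 when L < 220 − 140/m.

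- TDD 60: L < 220 − 84 = 136, so L between 130 and 136.
- TDD 75: L < 220 − 70 = 150, so L between 130 and 150.
- TDD 100: L < 220 − 46.7 = 173.3, so L between 130 and about 173.
- 10 percent step (m = 1/0.9): L < 220 − 126 = 94, which never triggers a decrease.

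If the earlier correction had reached only 200, one flat step predicts 220 − 2 × 20 = 180 at TDD 75 and 220 − 3 × 20 = 160 at TDD 100. There is no overshoot in that case, and the 10 percent step predicts 220 − 20/0.9 = 198.

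**No sharp line.** For a general starting BG, overshoot becomes possible when m > (BG − 80)/(BG − 130), that is TDD > 7500/(BG − 80). This is 75 U at BG 180, 62.5 U at BG 200 and 44 U at BG 250. No TDD cleanly separates a safe step from an unsafe one.

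**Proportional step.** A 10 percent change in ISF gives 1/0.9 = 1.11 (+11%) or 1/1.1 = 0.91 (−9%) at every TDD.

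**The case against.** Three arguments count against the point.

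First, 10 may have meant 10 percent, as in the adjacent bolus rule. That is possible. It would turn the repair into a clarification, but Table 3 does not say it, and a family or nurse reading the table would subtract 10.

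Second, the change is gated and watched. Staff advise it as needed, after most highs have repeated. The teach-back in the Visit III procedure covers the correction factor plan. Calls twice a week in the first month help calculate doses. Meter data are downloaded every third day and reviewed on the day they arrive. Families are told to call about any reading below 70 in the first treat-to-target week. The safety officer reviews hospital admissions and serious adverse events. These measures lower the likelihood of harm, and staff may well stop at an ISF falling from 15 to 5. But none supplies a numeric limit, and glucose monitoring detects a low only after the enlarged dose has been given. The hypoglycemia rationale in section 8 cites the 1 to 2 unit basal adjustment and the monitoring plan, and does not discuss the correction step.

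Third, overshoot depends on how near the earlier correction came to target. That is correct. Where it fell far short, a large step can be harmless or even helpful, as the example landing at 200 shows.

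**Conclusion.** The rule is wrong as written and should be fixed. On the flat reading the multiplier 150/(150 − TDD) is exact: 2 at 75 U, 3 at 100 U, and no valid result from 150 U. It assumes that ISF is still at its 1500-Rule value; the protocol does not say whether ISF is recalculated as TDD changes. That such TDDs occur is plausible from the protocol's dose range, but rests on assumed weights.

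The clinical harm is less certain than the arithmetic. A reader might infer that the rule will drive participants to profound hypoglycemia. The documents do not support that: such predictions come from linear extrapolation of near-miss corrections, and staff advice precedes each change. A reader might also infer that everyone entering by the type 1 route takes more than 2 U/kg/day, but that item is not clearly mandatory. Nor does the point touch the primary comparison, since both blinded arms follow the same insulin plan. The number of participants affected is unknown.

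**What to change.** In Table 3, state the unit and make the step proportional, for example 10 percent of the current ISF in both directions, in line with the meal bolus rule. Alternatively, keep an absolute step with a stated minimum ISF and a cap on the dose change per step. The clinical team should confirm the size against the TDDs the protocol allows. Update any family material that reproduces Table 3.

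The cost is one table amendment and that update, with no extra visits, participants or data. The downside is slower correction titration. The loss of speed is largest at high TDD (1.11 instead of 3 per step at 100 U) and small at low TDD (1.11 instead of 1.19 at 24 U). The clinical team should weigh this, because the slowing falls on the more insulin-resistant participants.

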**Table 2. Titration Algorithm for Long-acting insulin analog (Detemir)**

| **Average FPG of 3 consecutive days** | **Recommended Long-acting insulin analog dose adjustments** |
| --- | --- |
| <90 mg/dL (5.0 mmol/L) | -2 units of detemir |
| 90-120 mg/dl (5.0-6.7 mmol/L) | No adjustments |
| > 120 mg/dL (>6.7 mmol/L) | +2 units of detemir |

**Follow up phone calls:** Subjects will be followed with twice weekly phone calls in the first month of enrollment to assess compliance and to help calculate insulin titration doses and make necessary dose adjustments. After the first month of study, subjects will be contacted every 2 weeks until the end of the study. We will also instruct the families to call the diabetes line during the first week of treat to target regimen if any fingerstick blood glucose reading is <70 mg/dL or two readings of >250 mg/dL.

**Downloading of Glucometer reading:**Each subject will be provided with a glucometer. They will be instructed on how to download the glucose readings to a computer. They will be advised to download their glucometer readings on every third day and email or fax the downloaded data to a contact number or email address provided by the investigators for review and a follow up recommendation.

All participants will return to the clinic at +3 and +6 months for interim visits and at +9 months for study conclusion.

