Following the blood draw, each subject will be started on a patient-directed, treat-to-target insulin regimen. All participants will be on multiple daily injections (MDI) consisting of once daily injection of long acting insulin analog, detemir, meal time insulin boluses with aspart, and a correction factor for insulin to ensure euglycemia between meals. All insulins will be administered subcutaneously using a flexpen device.

Randomization for this study will be done by the Investigational Drug Services (IDS) using www.randomization .com. Randomization will be 1:1 (metformin : placebo) and will be blocked for every 10 subjects. Pharmacy will maintain blinding information and PI will contact IDS for emergency unblinding. IDS is available 24 hours a day and 7 days of the week via pager. Call schedule is available on OurNet.

Subjects will be followed with twice weekly phone calls in the first month of enrollment to assess compliance and to help calculate insulin titration doses and make necessary dose adjustments. After the first month of study, subjects will be contacted every 2 weeks until the end of the study.

Each subject will be provided with a **glucometer** and will be instructed on how to download the glucose readings to a computer every third day and email or fax the downloaded data to a contact number or email address provided by the investigators for review and a follow up recommendation. Investigators will review glucometer readings on the same day that they are emailed or faxed. All participants will return to the clinic at +3 and +6 months for interim visits and at +9 months for study conclusion.

b. Inclusion/Exclusion Criteria - As appropriate, explain what steps will be taken to insure that subjects meet the criteria (e.g. healthy, not pregnant, etc).

Subjects who meet the following criteria will be enrolled in the study:

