**Assessments for Safety**

**Hypoglycemia**: The major safety concern for this study, as in the general management of diabetes, is hypoglycemia. For this study, the following classification of hypoglycemia will be used: (a) **major**: hypoglycaemic event requiring a third party assistance, (b) **minor**: self measured plasma glucose level of ≤ 60 mg/dL, (c) **symptoms only**: self-measured plasma glucose of > 60 mg/dL or no measurement during the episode, (d) **nocturnal**: self-measured plasma glucose of ≤ 60 mg/dL occurring between 11 pm and 6 am. Hypoglycemia will be monitored by self-measured plasma glucose by checking blood glucose before meals, at bedtime, and at 3 a.m. We will evaluate the glycemic profile every third day by reviewing the data sent in to our office by the participants’ families via fax or email. Insulin dose adjustments, and other appropriated suggestions will be made based on these data. We will ensure that participants maintain a bedtime blood glucose level of >100 mg/dL before going to sleep. It is the standard of care for patients to check their blood sugar level before bed and if it is less than 100 mg/dL to eat a snack and recheck their blood sugar to make sure that it is over 100 before going to bed.

Participants will also check 3AM blood glucose twice weekly and also on 2 consecutive nights following changes to their long-acting insulin dose.

**Renal and liver function tests**: We will obtain liver function studies, and creatinine levels at the beginning and at the end of the study.

We will monitor **weight, body mass index, and vital signs** at each visit.

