Treat to target regimen and oral medications will not be initiated simultaneously. Our protocol is to initiate and familiarize the patients with all aspects of treat to target regimen during the run-in phase of the study without adding metformin or placebo. Thereafter, we will introduce the oral agents. Therefore, subjects will have ample time to work with treat to target regimen before receiving oral agents.

We do not anticipate an increased frequency or risk of hypoglycemia with the treat to target regimen because treat to target regimen is not a unidirectional model of care. It is based on a bidirectional flexible model that allows the patient to subtract or add 1-2 units to his/her long acting insulin dose depending on his 3-day average fasting blood glucose level. We have also built in a close follow up and monitoring plan for this study. For example, the frequent phone calls during which we will review finger stick blood glucose readings with the family and the fact that the families will fax or email finger stick blood glucose readings to us twice weekly will ensure very close monitoring of blood glucose excursions throughout the study duration. We will also ensure that participants maintain a bedtime blood glucose level of >100 mg/dL before going to sleep. Participants will also check 3AM blood glucose twice weekly and also on 2 consecutive nights following changes to their long-acting insulin dose. We will also instruct the families to call the diabetes line during the first week of treat to target regimen if any fingerstick blood glucose reading is <70 mg/dL or two readings of >250 mg/dL.

We also do not anticipate the adjunctive metformin therapy to cause hypoglycemia as we will be titrating basal insulin doses to the prevailing glycemia, and will reduce the dose of basal insulin if there is evidence of incipient hypoglycemia.

Finally, we have included a Hypoglycemia Monitoring Table to enable participants document their low sugar reactions in an effective way so we can address these reactions promptly.

b. Explain what steps will be taken to protect against its occurrence, minimizing the harm, methods for early detection of harm, and what procedures will be followed to avoid serious injury (e.g. withdraw from study or dose reduction).

Study Safety Officer: [name].

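### The family-applied detemir table acts only on a 3-day mean, so a single hypoglycaemic fasting value can be followed by a held or raised basal dose

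*Protocol*

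**What the plan says.** Under Visit III, part C (basal insulin), "Subjects will titrate their long-acting insulin analog (detemir) dose every third day", aiming at a fasting glucose of 90-120 mg/dL. The algorithm is the second of two tables numbered 2. Its only input is "Average FPG of 3 consecutive days": a mean below 90 mg/dL gives -2 units, 90-120 gives no adjustment, and above 120 gives +2 units. No row or note deals with an individual low value.

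The risks section describes the same rule. The patient can "subtract or add 1-2 units to his/her long acting insulin dose depending on his 3-day average fasting blood glucose level", and this two-way flexibility is one reason given for expecting no extra hypoglycaemia. The same section says the team "will reduce the dose of basal insulin if there is evidence of incipient hypoglycemia". It gives no glucose value, step size or timing.

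Bolus insulin is handled differently. Part A cuts the preceding premeal bolus by 10% after a single low, on the ground that "Changing this bolus dose the very next day will prevent a recurrence of hypoglycemia". The readings it names are those before lunch, dinner and bedtime.

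Under Assessments for Safety, minor hypoglycaemia is a "self measured plasma glucose level of ≤ 60 mg/dL".

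**The concern.** A mean of three values can hide one low behind two highs. If a family follows the table as printed, the basal dose may stay the same or rise directly after a fasting value that the protocol defines as hypoglycaemia. That sits badly with the commitment to reduce basal insulin, which a family holding only the table cannot apply because it has no threshold. It also leaves the basal rule less cautious than the bolus rule, and no reason is given for the difference. The participants are 10 to 18 years old and titrate for nine months, so the stake is avoidable hypoglycaemia.

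**Working it through.** **Inputs** (all from the protocol): cut-offs of 90 and 120 mg/dL on the 3-day mean, with steps of -2, 0 and +2 units (detemir titration table); titration every third day (Visit III, part C); hypoglycaemia at 60 mg/dL or below (Assessments for Safety); call-in value of 70 mg/dL (Follow up phone calls); compliance criterion of at least 6 downloads a month (Subject Compliance).

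**The table's own figures.** Dividing by 18.016, 90 mg/dL is 5.0 mmol/L and 120 mg/dL is 6.7 mmol/L, as printed.

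**Formula.** With one low value L and the other two averaging m, the mean is (L + 2m)/3. It reaches 90 at m = (270 - L)/2 and 120 at m = (360 - L)/2.

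| Low value L (mg/dL) | -2 units if m is | No change if m is | +2 units if m is |
|---|---|---|---|
| 69 | below 100.5 | 100.5-145.5 | above 145.5 |
| 60 | below 105 | 105-150 | above 150 |
| 55 | below 107.5 | 107.5-152.5 | above 152.5 |
| 50 | below 110 | 110-155 | above 155 |

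**Worked cases.**
- 60, 104, 104: 268/3 = 89.3, so -2 units. Three values of 104 would give no change, so here the single low produced the reduction.
- 60, 120, 120: 300/3 = 100, so no change.
- 60, 160, 160: 380/3 = 126.7, so +2 units.
- 55, 110, 210: 375/3 = 125, so +2 units.

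**Is team review assured before each step?** Titration every third day is about 30/3 = 10 steps a month. Six downloads a month count as compliant, so about 10 - 6 = 4 steps a month could pass without a fresh download in a compliant family. Nothing in the protocol tells families to wait for the team's reply before changing the dose.

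**Size of one step.** Part C aims at basal insulin of 0.3-0.8 U/kg/day, or more if needed. Body weight is not given; I assume 40-90 kg.
- 40 kg: 12-32 U/day, so 2 units is 16.7% down to 6.3%.
- 90 kg: 27-72 U/day, so 2 units is 7.4% down to 2.8%.
- Type 1 entry route (more than 2 U/kg/day in total, split 1:1): basal is above 1 U/kg, so 2 units is below 5% at 40 kg and below 2.3% at 90 kg.

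**The case against.** The best defence is that the table does not stand alone. Its column is headed as recommended adjustments, and several safeguards surround it:
- Downloads are requested every third day, the same interval as titration, and "Investigators will review glucometer readings on the same day that they are emailed or faxed"; the team then adjusts doses. The risks section also has readings sent twice weekly.
- In the first month, twice-weekly calls help work out titration doses.
- Families must call the diabetes line "during the first week of treat to target regimen if any fingerstick blood glucose reading is <70 mg/dL".
- Bedtime glucose must exceed 100 mg/dL, with a snack and recheck if it does not. Detemir is given at bedtime, so this check falls at the time of dosing.
- 3 AM glucose is checked twice weekly and on two nights after a change in the long-acting dose.
- Increasing hypoglycaemia is a withdrawal criterion.

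These measures reduce the risk, and a reader should not infer that hypoglycaemia goes unmonitored. They do not close the gap. The call-in covers one week of nine months, and calls fall to every two weeks after the first month. Review at every step is not assured. The bedtime and 3 AM checks carry no stated detemir action.

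A reader might also infer that the downward step never responds to an isolated low. The arithmetic does not support this: with a low of 60 mg/dL the table does reduce the dose whenever the other two values average below 105. Nor should the point be pressed to readings below 30 mg/dL without noting that the Summary of Procedure has each severe episode reviewed immediately, though it states this for patients with more than three in the preceding month.

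Finally, the family summary sheet and the Hypoglycemia Monitoring Table are not shown and may already contain a rule for single lows. That part of the objection stands and limits the conclusion to what is on the page.

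**Conclusion.** The point holds as a matter for clarification on participant safety. As printed, the table can hold or raise detemir after a fasting value the protocol calls hypoglycaemia. For a low of 60 mg/dL this happens when the other two values average 105-150 (hold) or above 150 (raise). No safeguard shown bars that increase.

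The cut-offs are exact and assume no glucose distribution. For the same reason, how often such triples occur cannot be derived. One step is about 3-17% of basal insulin under the assumed weights and less for the type 1 entry route, so the concern is the direction of the step after a low more than its size. A reader might take this as a threat to the trial's result. The documents do not support that: the rule is the same in both blinded arms and does not bias the primary comparison.

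**What to change.** Add one line to the detemir titration table and to the family summary sheet: any fasting or 3 AM reading at or below a set threshold within the 3-day window bars an increase whatever the mean, and prompts a same-day call to the team. Either of the protocol's own values could serve, 60 mg/dL or below (minor hypoglycaemia) or below 70 mg/dL (the first-week call-in); the clinical team should confirm which.

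Leave any basal reduction to the team after it has reviewed the cause, since the Summary of Procedure lists causes such as a missed meal or unplanned exercise that may need no basal cut. If the summary sheet or the Hypoglycemia Monitoring Table already holds such a rule, repeat it in the titration table.

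The cost is slightly slower titration and some extra calls, under the same rule in both arms. The readings are already part of the monitoring plan.
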